**Pregnancy**

Erlotinib has been shown to cause maternal toxicity with associated embryo/fetal lethality and abortion in rabbits when given at doses that result in plasma drug concentrations of approximately 3 times those in humans (AUCs at 150 mg daily dose). When given during the period of organogenesis to achieve plasma drug concentrations approximately equal to those in humans, based on AUC, there was no increased incidence of embryo/fetal lethality or abortion in rabbits or rats. However, female rats treated with 30 mg/m^2/day or 60 mg/m^2/day (0.3 or 0.7 times the clinical dose, on a mg/m^2 basis) of erlotinib prior to mating through the first week of pregnancy had an increase in early resorptions that resulted in a decrease in the number of live fetuses. No teratogenic effects were observed in rabbits or rats. There are no adequate and well-controlled studies in pregnant women using TARCEVA. Women of childbearing potential should be advised to avoid pregnancy while on TARCEVA. Adequate contraceptive methods should be used during therapy, and for at least 2 weeks after completing therapy. Treatment should only be continued in pregnant women if the potential benefit to the mother outweighs the risk to the fetus. If TARCEVA is used during pregnancy, the patient should be apprised of the potential hazard to the fetus or potential risk for loss of the pregnancy.

**Precautions****Hepatotoxicity**

Asymptomatic increases in liver transaminases have been observed in TARCEVA treated patients; therefore, periodic liver function testing (transaminases, bilirubin, and alkaline phosphatase) should be considered. Dose reduction or interruption of TARCEVA should be considered if changes in liver function are severe.

**Patients with Hepatic Impairment**

*In vitro* and *in vivo* evidence suggest that erlotinib is cleared primarily by the liver. Therefore, erlotinib exposure may be increased in patients with hepatic dysfunction

**Elevated International Normalized Ratio and Potential Bleeding**

International Normalized Ratio (INR) elevations and infrequent reports of bleeding events including gastrointestinal and non-gastrointestinal bleedings have been reported in clinical studies, some associated with concomitant warfarin administration. Patients taking warfarin or other coumarin-derivative anticoagulants should be monitored regularly for changes in prothrombin time or INR.

**Carcinogenesis, Mutagenesis, Impairment of Fertility**

Erlotinib has not been tested for carcinogenicity. Erlotinib has been tested for genotoxicity in a series of *in vitro* assays (bacterial mutation, human lymphocyte chromosome aberration, and mammalian cell mutation) and an *in vivo* mouse bone marrow micronucleus test and did not cause genetic damage. Erlotinib did not impair fertility in either male or female rats.

**Nursing Mothers**

It is not known whether erlotinib is excreted in human milk. Because many drugs are excreted in human milk and because the effects of TARCEVA on infants have not been studied, women should be advised against breast-feeding while receiving TARCEVA therapy.

**Pediatric Use**

The safety and effectiveness of TARCEVA in pediatric patients have not been studied.

**Geriatric Use**

Of the total number of patients participating in the randomized NSCLC trial, 62% were less than 65 years of age, and 38% of patients were aged 65 years or older. The survival benefit was maintained across both age groups. In the pancreatic cancer study, 53% of patients were younger than 65 years of age and 47% were 65 years of age or older. No meaningful differences in safety or pharmacokinetics were observed between younger and older patients in either study. Therefore, no dosage adjustments are recommended in elderly patients.

## 2.2 NSCLC

Non-small cell lung cancer is the commonest cause of cancer mortality in Singapore. Up to 70% of patients are diagnosed with advanced stage IIIB and IV disease at presentation and significant proportion of patients with resected disease eventually relapse and die of disease. In Asia, the number of patients with lung cancer is expected to grow given the increasing prevalence of smoking in the local populations. Conventional palliative chemotherapy has reached a plateau in survival benefit and there is a need for novel agents for treatment of this disease. The introduction of EGFR TK-I into the treatment of NSCLC gives additional improvement in survival in a select percentage of patients only. There is therefore a clear need for new approaches in treating metastatic NSCLC patients in the salvage setting as all “classical” cytotoxic or targeted drugs provide the same range of efficacy.

Erlotinib is currently approved for use in the salvage setting as monotherapy for non-small cell lung carcinoma. However, response rates are around 10% in a large phase III study (1). Equivalent response rates are achieved using conventional cytotoxics in the salvage setting (2-4). Combining an oral cytotoxic with an oral targeted therapy provides the convenience and cost-savings of oral therapy with the potential of increasing response rates.

## 2.3 Rational

Additive or supradadditive activity of an EGFR TK-I with vinorelbine has been demonstrated in-vitro (5). Clinical synergism has also been described between gefitinib and vinorelbine in NSCLC (6). The use of cytotoxics in a metronomic schedule has not been well investigated in the clinical setting despite emerging pre-clinical data. Using an established oral cytotoxic such as oral vinorelbine in a metronomic dose-schedule is attractive due to the oral route of administration. Preclinical studies have shown that by using cytotoxics in a low-dose protracted manner, endothelial cells are preferentially affected via inhibition of proliferation and induction of apoptosis (7). In addition to this anti-angiogenic mechanism, an anti-vasculogenic process may also be involved that acts by reducing circulating endothelial progenitor mobilization and viability (8). Moreover, it has also been shown that tumours that were selected for high levels of acquired resistance to cytotoxics can be induced to respond by using metronomic doses of chemotherapy (9, 10).

Continuous administration of metronomic oral vinorelbine, given three times a week, has been reported as feasible and well tolerated at doses up to 180 mg total dose per week. Early results showed activity against refractory solid tumors such as renal cancer, NSCLC, ovarian cancer, prostate cancer, unknown primary and Kaposi sarcoma (Briasoulis et al EORTC-NCI-AACR 2006). Eighty patients (39 female and 41 male, median age 58, median PS 1) were treated in this study with a variety of progressive refractory solid cancers and were treated at the dose range of 20 mg (16 pts), 30 mg (17 pts), 40 mg (26 pts), 50 mg (13 pts), 60 mg (6 pts) and 70 mg (2 pts) TTW. Dose limiting toxicity occurred in 2 patients at the 60 mg dose level (leucopenia grade 4 on the 14th week of treatment and epistaxis on the 9th week treatment). Median duration of treatment was 19 weeks (range 4 to 85+ weeks) and corresponded to time to progression, since no withdrawals from therapy were due to toxicity. Objective tumor response was documented in 8 among 52 patients in renal cancer, NSCLC, ovarian cancer, prostate cancer, unknown primary and Kaposi sarcoma while 32% of treated patients had disease control for at least 6 months. A similar metronomic dosing schedule was also shown to be safe and feasible up to 50 mg three times a week (11).

However, determining the optimal metronomic dose of a cytotoxic agent is challenging as optimal antiangiogenic activity would likely be below the maximum tolerated dose (MTD). Using levels of circulating endothelial cells (CECs) and circulating endothelial progenitor cells (CEPs) has been shown to good surrogate

pharmacodynamic marker to monitor antiangiogenic activity of a drug (13).

This phase I study combines erlotinib and oral vinorelbine on two different schedules. The conventional schedule vinorelbine (CSV) aims to determine the MTD of conventional schedule of oral vinorelbine given on days 1 and 8 every 21 days plus daily erlotinib and the metronomic schedule vinorelbine (MSV) aims to determine the optimal metronomic dose of vinorelbine given 3 times a week plus daily erlotinib.

The objectives are:

- a) To assess whether combination of oral vinorelbine and erlotinib is safe and feasible
- b) To determine dosing of oral vinorelbine on a metronomic schedule leading to anti-angiogenesis as demonstrated by CEP/CEC assays

### 3. PATIENT SELECTION

#### 3.1 Eligibility Criteria

3.1.1 Patients must have histologically or cytologically confirmed *NSCLC*

3.1.2 *At least one or two prior lines of chemotherapy for metastatic disease or locally advanced unresectable disease.* There should be at least 4 weeks since prior chemotherapy or radiation therapy or 6 weeks if the last regimen included BCNU or mitomycin C

3.1.3 Age  $\geq$  21 years.

3.1.4 ECOG performance status  $<2$  (Karnofsky  $>60\%$ , see Appendix A).

3.1.5 Life expectancy of greater than 3 months

3.1.6 Patients must have normal organ and marrow function as defined below:

- |                             |                                                                                               |
|-----------------------------|-----------------------------------------------------------------------------------------------|
| – leukocytes                | $>3,000/\text{mcL}$                                                                           |
| – absolute neutrophil count | $>1,500/\text{mcL}$                                                                           |
| – platelets                 | $>100,000/\text{mcL}$                                                                         |
| – total bilirubin           | within normal institutional limits                                                            |
| – AST(SGOT)/ALT(SGPT)       | $<2.5 \times$ institutional upper limit of normal                                             |
| – creatinine                | within normal institutional limits                                                            |
| OR                          |                                                                                               |
| – creatinine clearance      | $>60 \text{ mL/min/1.73 m}^2$ for patients with creatinine levels above institutional normal. |

3.1.7 The effects of Oral Vinorelbine on the developing human fetus are unknown. For this reason and because vinca alkaloids as well as other therapeutic agents used in this trial are known to be teratogenic, women of

child-bearing potential and men must agree to use adequate contraception (hormonal or barrier method of birth control; abstinence) prior to study entry and for the duration of study participation. Should a woman become pregnant or suspect she is pregnant while participating in this study, she should inform her treating physician immediately.

- 3.1.8 Ability to understand and the willingness to sign a written informed consent document.

## 3.2 Exclusion Criteria

- 3.2.1 Patients who have had chemotherapy or radiotherapy within 4 weeks (6 weeks for nitrosoureas or mitomycin C) prior to entering the study or those who have not recovered from adverse events due to agents administered more than 4 weeks earlier.
- 3.2.2 Patients may not be receiving any other investigational agents.
- 3.2.3 Patients who have received previous vinorelbine or oral EGFR tyrosine kinase inhibitors
- 3.2.4 Patients with *progressive* brain metastases should be excluded from this clinical trial because of their poor prognosis and because they often develop progressive neurologic dysfunction that would confound the evaluation of neurologic and other adverse events. *However patients are eligible if they have brain metastases that have been treated with whole brain radiotherapy and are stable and not on corticosteroids.*
- 3.2.5 History of allergic reactions attributed to compounds of similar chemical or biologic composition to Oral Vinorelbine or other agents used in study.
- 3.2.6 Prior and / or concomitant treatment with drugs known to induce or inhibit cytochrome P450 3A4, CYP1A1 & CYP1A2 : phenytoin, carbamazepine, barbiturates, rifampicine, imidazole antifungals (such as ketoconazole, fluconazole, itraconazole, metronidazole), omeprazole and ritonavir *within 1 week of starting protocol treatment.*
- 3.2.7 Significant malabsorption syndrome or disease affecting the gastro-intestinal tract function
- 3.2.8 Uncontrolled intercurrent illness including, but not limited to, ongoing or active infection, symptomatic congestive heart failure, unstable angina pectoris, cardiac arrhythmia, or psychiatric illness/social situations that would limit compliance with study requirements.
- 3.2.9 Pregnancy or breast feeding or women of child-bearing potential not using effective contraception.

3.2.10 HIV-positive patients on combination antiretroviral therapy are ineligible because of the potential for pharmacokinetic interactions with Oral Vinorelbine. In addition, these patients are at increased risk of lethal infections when treated with marrow-suppressive therapy. Appropriate studies will be undertaken in patients receiving combination antiretroviral therapy when indicated.

3.2.11 History of organ allograft

3.2.12 Patients with evidence or history of bleeding diathesis or coagulopathy

3.2.13 Serious, non-healing wound, ulcer, or bone fracture

3.2.14 Because of interaction risk on CYP3A4, patients with concomitant treatments with vitamin K antagonists such as phenprocoumon or warfarin

### 3.3 **Inclusion of Women and Minorities**

Both men and women of all races and ethnic groups are eligible for this trial.

## 4. **REGISTRATION PROCEDURES**

*N.A*

## 5. **TREATMENT PLAN**

### 5.1 **Agent Administration**

This is a Phase I Dose-Finding Study examining the combination of vinorelbine/erlotinib. The MTD approach will be used for both phase I schedules as shown in table below. Treatment will be administered on an outpatient basis. Oral vinorelbine will be started according to two different schedules (see tables below) 2 days before starting erlotinib. A “ping-pong” phase 1 design is employed allowing each schedule to accrue sequentially at each dose level (see figure below). This design expedites accrual without compromising safety and monitoring. All accrual will start at dose level 1. When CSV level 1 has completed accrual, MSV level 1 will start accrual while waiting for CSV level 1 patients to complete their first cycle of treatment. When MSV level 1 has completed accrual, CSV level 2 will begin and the cycle repeats itself till dose level 5 or unless DLT is reached for one schedule, and so on till DLT or dose level 5 reached. Once the MTD in one schedule is reached before level 5, the other schedule will continue till the MTD or level 5 is reached

| Dose Escalation Schedule                                                                            |                                                                     |                                                      |            |
|-----------------------------------------------------------------------------------------------------|---------------------------------------------------------------------|------------------------------------------------------|------------|
| Erlotinib
100 mg
(start 2 days after
vinorelbine for
cycle 1)                   | Dose                                                                |                                                      |            |
|                                                                                                     | CSV                                                                 | MSV                                                  | Dose Level |
|                                                                                                     | Vinorelbine (mg/m 
on D1,D8 every 21
days)        | Vinorelbine
(mg/week)                             |            |
|                                                                                                     | 30                                                                  | 80                                                   | Level -1   |
|                                                                                                     | 40                                                                  | 100                                                  | Level 1    |
|                                                                                                     | 50                                                                  | 120                                                  | Level 2    |
|                                                                                                     | 60                                                                  | 140                                                  | Level 3    |
|                                                                                                     | 70                                                                  | 160                                                  | Level 4    |
|                                                                                                     | 80                                                                  | 180                                                  | Level 5    |
| Erlotinib
150 mg
(only in the
absence of DLT at
dose level 5 of
vinorelbine) | No DLT at dose level
5 of vinorelbine
(80 mg/m  ) | No DLT at dose level
5 of vinorelbine
(180 mg) |            |

Escalation of Erlotinib dose to 150 mg OM will only start if level 5 oral vinorelbine is reached without dose-limiting toxicities with Erlotinib 100 mg OM in each schedule.

The optimal anti-angiogenic dose of oral vinorelbine given in metronomic schedule will be determined from the Circulating Endothelial Cells/Circulating Endothelial Progenitors (CEC/CEP) assays correlations.

Efficacy will be assessed every 2 cycles during maintenance treatment. Each cycle will last 21 days with a window period of 7 days. Patients on the conventional schedule of vinorelbine who respond or have stable disease, vinorelbine will be stopped after 6 cycles and erlotinib continued. Patients on the metronomic schedule of vinorelbine who respond will continue on both vinorelbine and erlotinib.

Reported adverse events and potential risks for Oral Vinorelbine and Erlotinib are described in Section 5.2. Appropriate dose modifications for Oral Vinorelbine and Erlotinib are described in Section 6. No investigational or commercial agents or therapies other than those described below may be administered with the intent to treat the patient's malignancy.

| REGIMEN DESCRIPTION |                                                                                                                                                                                                  |                                             |              |                                                                                                                                      |                     |
|----------------------------|--------------------------------------------------------------------------------------------------------------------------------------------------------------------------------------------------|---------------------------------------------|--------------|--------------------------------------------------------------------------------------------------------------------------------------|---------------------|
| Agent               | Premedications; Precautions                                                                                                                                                               | Dose                                 | Route | Schedule                                                                                                                      | Cycle Length |
| Vinorelbine                | Both erlotinib and vinorelbine will be given after prophylactic administration of antiemetics (preferably 5-HT 3 antagonist) on Day 1 (except for Cycle 1) and on Day 8 of each cycle | Dose as appropriate for assigned dose level | Oral         | Conventional Schedule: Day 1 and 8 of each cycle
Metronomic Schedule: D1,3,5 every 7 days for 3 weeks of each cycle | 21 days (3 wks)     |
| Erlotinib                  | To be taken whole half hour before breakfast                                                                                                                                                     | Dose as appropriate for assigned dose level | Oral         | Daily                                                                                                                                |                     |

In cases where the patient's BSA > or equal to 2.0, oral Navelbine dose should not exceed twice the dose/m^2 (e.g. 120 mg for 60 mg/m^2, and 160 mg for 80 mg/m^2) per week. In cases where the BSA < or equal to 1.4, these patients will not be recruited into the metronomic arm – this is for patient safety to avoid excessive dose.

The standard “3+3” rule will be employed for dose escalation. Three patients will be accrued at the starting dose levels. If no dose limiting toxicities greater than grade 2 were observed, 3 patients would be entered at the next dose level. If, at any dose level, one of the first 3 patients experiences a DLT, 3 additional patients will be entered at that dose level. If 2 out of 6 patients experience dose-limiting toxicities at this dose level, dose escalation will cease.

The maximally tolerated dose (MTD) will be defined as one dose level below that at which 2 or more patients experienced DLT. If DLT is observed at initial level of either schedule, an additional 3 patients will be accrued at the –1 level. If DLT is observed at this level, the trial will be terminated.

A patient who experiences any DLT will be allowed to continue treatment with a one dose level reduction if the toxicity resolves within 14 days. If this patient experiences a DLT at the lowered dose level, study treatment will be stopped for this patient.

No intra-patient dose escalation will be allowed. Re-entry of a patient accrued at a lower dose into a higher dose cohort will not be allowed. Accrual rate is expected to be 3-4 patients per month. Dose escalation will proceed within each cohort according to the following schedule.

| Number of Patients with DLT at a Given Dose Level                             | Escalation Decision Rule                                                                                                                                                                                                                                                                                                                                                                                                                                           |
|-------------------------------------------------------------------------------|--------------------------------------------------------------------------------------------------------------------------------------------------------------------------------------------------------------------------------------------------------------------------------------------------------------------------------------------------------------------------------------------------------------------------------------------------------------------|
| 0 out of 3                                                                    | Enter 3 patients at the next dose level.                                                                                                                                                                                                                                                                                                                                                                                                                           |
| $\geq 2$                                                                      | Dose escalation will be stopped. This dose level will be declared the maximally administered dose (highest dose administered). Three (3) additional patients will be entered at the next lowest dose level if only 3 patients were treated previously at that dose.                                                                                                                                                                                                |
| 1 out of 3                                                                    | Enter at least 3 more patients at this dose level. 
 
• If 0 of these 3 patients experience DLT, proceed to the next dose level.
 
• If 1 or more of this group suffer DLT, then dose escalation is stopped, and this dose is declared the maximally administered dose. Three (3) additional patients will be entered at the next lowest dose level if only 3 patients were treated previously at that dose.
 
 |
| $\leq 1$ out of 6 at highest dose level below the maximally administered dose | This is generally the recommended phase 2 dose. At least 6 patients must be entered at the recommended phase 2 dose.                                                                                                                                                                                                                                                                                                                                               |

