### Absorption and Distribution

Bioavailability of erlotinib following a 150 mg oral dose of TARCEVA is about 60% and peak plasma levels occur 4 hrs after dosing. Food increases bioavailability substantially, to almost 100%. Following absorption, erlotinib is approximately 93% protein bound to albumin and alpha-1 acid glycoprotein (AAG). Erlotinib has an apparent volume of distribution of 232 liters.

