## **Dosage and Administration**

### **Non-Small Cell Lung Cancer**

The recommended daily dose of TARCEVA is 150 mg taken at least one hour before or two hours after the ingestion of food. Treatment should continue until disease progression or unacceptable toxicity occurs. There is no evidence that treatment beyond progression is beneficial.

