### **Pancreatic Cancer**

The recommended daily dose of TARCEVA is 100 mg taken at least one hour before or two hours after the ingestion of food, in combination with gemcitabine (see the gemcitabine package insert). Treatment should continue until disease progression or unacceptable toxicity occurs.

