##### Erlotinib

Erlotinib will commence on day 3 to allow PK profiling of vinorelbine alone.

Pharmacokinetic analysis for erlotinib and its metabolite, OSI-420 will be done on days 3

(after the first dose) and 10 (at steady state).

Day 3: 0hr (predose), 1hr, 2hr, 4hr, 6hr, 8hr, 24hr.

Day 10: Steady state erlotinib pharmacokinetics will be evaluated on day 10 at the following time points: 0 hr (prior to dosing), 1hr, 2hr, 4hr, 6hr, 8hr, 24hr.

A single steady state trough level of erlotinib will be taken on day 22 of every cycle

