## **13.1 Analysis**

- The primary aim of this study is to determine the dose limiting toxicities of oral vinorelbine combined with erlotinib and the maximal tolerated dose (MTD) of this drug combination in patients with non-small cell lung cancer. The toxicity profile will be graded as described above and reported with the corresponding dose level.
- The MTD will be dose at which less than 2 DLTs occur. Steady state plasma drug

concentrations, area under the curve values, volume of distribution and clearance of oral vinorelbine and erlotinib in each patient will be calculated and correlated with dose. These quantities will be summarized for all patients.

- Response rates (Complete response, partial response, stable disease) to study treatment will be described based on RECIST criteria and summarized by dose. Overall survival will be measured from registration to death and analyzed by the Kaplan-Meier method.
- Exploratory analysis of known functional SNPs in the transporter genes will be described in relation to dose and response. An exploratory analysis of the changes on CEC/CEP assessment of angiogenesis in each group would be performed.

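### Section 5.1 has erlotinib taken half an hour before breakfast, half the one-hour minimum in the protocol's own drug section, with no reason given

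*Protocol*

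**What the plan says.** The regimen description table in Protocol Section 5.1 instructs for erlotinib: "To be taken whole half hour before breakfast". No other meal-timing rule for erlotinib appears in the treatment plan. Section 5.1.2, headed Erlotinib, contains no instruction at all.

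The drug information in Section 2.1.2 differs. For non-small cell lung cancer, at 150 mg daily, the drug is to be "taken at least one hour before or two hours after the ingestion of food". For pancreatic cancer it reads: "The recommended daily dose of TARCEVA is 100 mg taken at least one hour before or two hours after the ingestion of food". Both doses used in the trial therefore carry the same one-hour minimum.

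The reason to fast is given under Absorption and Distribution in the same section. After a 150 mg dose, bioavailability "is about 60% and peak plasma levels occur 4 hrs after dosing", and then: "Food increases bioavailability substantially, to almost 100"%.

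Erlotinib exposure is also a study measurement. Section 9.1.2 samples erlotinib on days 3 and 10 ("Steady state erlotinib pharmacokinetics will be evaluated on day 10"), and Section 13.1 plans that "area under the curve values, volume of distribution and clearance of oral vinorelbine and erlotinib in each patient will be calculated".

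**The concern.** A shorter gap before a meal can only leave erlotinib exposure unchanged or raise it. The protocol treats food as a substantial influence on that exposure, yet halves the fasting interval it quotes without saying why. The rationale (Section 2.3), concomitant medication (5.3), pharmaceutical information (8.2) and pharmacokinetic (9.1.2) sections give neither a reason nor another rule.

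Two results depend on the dosing condition:

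- **The MTD.** Under Section 5.2 any grade 3 or 4 non-haematological toxicity in cycle 1 is a DLT, and Section 2.1.2 names rash and diarrhoea as the most common reactions to single-agent erlotinib. If exposure is raised, the MTD is set under that raised exposure.
- **The reported erlotinib AUC and clearance.** These would describe a meal condition other than the recommended one, and the protocol asks for no record of meal times on the sampling days.

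**Working it through.** The protocol states no figure for the effect of a meal 30 minutes after dosing, so there is nothing to reproduce and only bounds can be derived.

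**Inputs**

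- Interval in the regimen table (Section 5.1): 30 minutes before breakfast.
- Minimum interval in the drug section (2.1.2), at 150 mg and at 100 mg: 60 minutes before food.
- Bioavailability F (2.1.2): about 0.60 after 150 mg without food, almost 1.00 with food.
- Time to peak (2.1.2): 4 hours.

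**Assumptions**

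- The 60% figure is the fasted value. The text implies this by saying that food increases it.
- The 60% figure, given for 150 mg, also applies at 100 mg.
- Almost 100% is taken as 1.00, which makes the bounds slightly too wide.

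**Interval.** 30 / 60 = 0.50, so the ordered interval is half the recommended minimum.

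**Exposure relative to fasted.** Lower bound 1.00 (the meal has no effect). Upper bound 1.00 / 0.60 = 1.67 (full food effect).

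**Apparent clearance (CL/F) relative to fasted.** From 1.00 down to 0.60 / 1.00 = 0.60.

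**Absorbed dose, compared with 150 mg fasted (0.60 × 150 = 90 mg)**

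| Cohort | Absorbed, no food effect | Absorbed, full food effect | Ratio to 150 mg fasted |
|---|---|---|---|
| Erlotinib 100 mg | 0.60 × 100 = 60 mg | 1.00 × 100 = 100 mg | 60/90 = 0.67 to 100/90 = 1.11 |
| Erlotinib 150 mg | 0.60 × 150 = 90 mg | 1.00 × 150 = 150 mg | 90/90 = 1.00 to 150/90 = 1.67 |

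**Position within the bounds.** This cannot be determined. With the peak at 4 hours, a meal at 30 minutes and a meal at 60 minutes both come before it, so the time to peak does not show how much the extra half hour matters.

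**Scale.** Section 2.1.2 reports that ketoconazole raised erlotinib AUC by two thirds, the same ratio as the upper bound here (1 + 2/3 = 1.67), and exclusion criterion 3.2.6 names ketoconazole. A change of that size is one the protocol takes care to avoid, but the comparison holds for the upper bound only.

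**The case against.** The strongest case against is that this is a legitimate choice with no demonstrated harm. Section 2.1.2 is background: it reproduces labelled use and words the interval as a recommendation, and the 100 mg statement concerns pancreatic cancer. The treatment plan gives a single order, and a phase I protocol may depart from labelling, as this one does with its vinorelbine doses and schedules. The 1.67 ceiling contrasts fed with fasted dosing, whereas the real question is a meal at 30 against 60 minutes, which the protocol does not quantify. The rule is common to all cohorts, so dose-level comparisons are unaffected and any extra exposure is reflected in the DLT count. The listed pharmacokinetic objective concerns the effect of erlotinib on vinorelbine, and no comparison of erlotinib exposure with labelled conditions is planned. Finally, a half-hour rule is more specific than an open-ended minimum.

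Most of this stands and keeps the point minor. Sites are not confused, dose levels remain comparable, and the MTD is valid for the regimen as given. It does not remove the point. The vinorelbine departures are what the trial sets out to study, whereas a shorter fast serves no stated objective. Erlotinib AUC and clearance are planned outputs under Section 13.1 even though they are not the listed objective. A more specific interval is no advantage if it falls inside the period the protocol's drug section says to keep free of food.

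**Conclusion.** The point holds and is minor. The half-hour rule is half the protocol's own recommended minimum at both trial doses, and no reason is given. That much is certain from the text.

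The consequence is bounded but unknown: exposure 1.00 to at most 1.67 times fasted, and apparent clearance 1.00 to no lower than 0.60 times fasted, under the assumptions listed above. The true effect may be nil. Relative to 150 mg fasted, the 100 mg cohorts cannot exceed about 1.11 times, so the safety relevance lies mainly in the 150 mg cohort. That cohort is conditional: "Escalation of Erlotinib dose to 150 mg OM will only start if level 5 oral vinorelbine is reached without dose-limiting toxicities". What remains is that the MTD and the erlotinib pharmacokinetics would be reported under a meal condition other than the one the protocol recommends.

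**What to change.** In the Section 5.1 regimen table, change the erlotinib line for all cohorts to: *to be taken whole in the morning on an empty stomach, at least one hour before breakfast*. This keeps a single morning dosing condition. Optionally, record the meal time on pharmacokinetic days 3 and 10. If the half hour is deliberate, a sentence giving the reason would at least close the gap in explanation.

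The cost is one table line and slightly less convenient dosing, plus one case report form field on two days if meal times are recorded. On shared dosing days vinorelbine can still be taken with breakfast, in line with the recommendation in Section 2.1.1 that it be taken with food. Sample size, cohorts and planned analyses do not change.
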